# Effectiveness of phototherapy incorporated into an exercise program for osteoarthritis of the knee: study protocol for a randomized controlled trial

**DOI:** 10.1186/1745-6215-15-221

**Published:** 2014-06-11

**Keywords:** Phototherapy, Osteoarthritis of the knee, Postural balance, Lower limb strength, Physical therapy modalities

## Abstract

**Background:**

Osteoarthritis is a chronic disease with a multifactor etiology involving changes in bone alignment, cartilage, and other structures necessary to joint stability. There is a need to investigate therapeutic resources that combine different wavelengths as well as different light sources (low-level laser therapy and light-emitting diode therapy) in the same apparatus for the treatment of osteoarthritis. The aim of the proposed study is to analyze the effect of the incorporation of phototherapy into a therapeutic exercise program for individuals with osteoarthritis of the knee.

**Methods/Design:**

A double-blind, controlled, randomized clinical trial will be conducted involving patients with osteoarthritis of the knee. Evaluations will be performed using functional questionnaires before and after the treatment protocols, in a reserved room with only the evaluator and participant present, and no time constraints placed on the answers or evaluations. The following functional tests will also be performed: stabilometry (balance assessment), dynamometry (muscle strength of gluteus medius and quadriceps), algometry (pain threshold), fleximeter (range of motion), timed up-and-go test (functional mobility), and the functional reach test. The participants will then be allocated to three groups through a randomization process using opaque envelopes: exercise program, exercise program + phototherapy, or exercise program + placebo phototherapy, all of which will last for eight weeks.

**Discussion:**

The purpose of this randomized clinical trial is to analyze the effect of the incorporation of phototherapy into a therapeutic exercise program for osteoarthritis of the knee. The study will support the practice based on evidence to the use of phototherapy in individuals with a diagnosis of osteoarthritis of the knee. Data will be published after the study is completed.

**Trial registration:**

The protocol for this study has been submitted to Clinical Trials, registration number NCT02102347, on 29 March 2014.

## Background

Osteoarthritis (OA) is a chronic condition of the joints, the most commonly affected of which is the knee. This condition is characterized by joint pain and in more advanced stages, joint deformities, contracture, and muscle atrophy leading to severe disability. Poor bone alignment, ligament injuries, and meniscal tears that lead to cartilage wear due to excessive impact and joint instability seem to be strongly correlated with the origin of this condition [1,2]. These factors, together with the increase in pain and diminished function, create difficulties in executing functional activities and can compromise postural stability, leading to a greater risk of falls [3].

Non-steroidal anti-inflammatory drugs (NSAIDs) are the first line of treatment in cases of OA to relieve pain and inflammation [1]. More recently, chondroitin and glucosamine have been used, which are essential components to cartilage formation but have not yet demonstrated consistent results regarding pain reduction and slowing down the narrowing of the joint space [4]. Indeed, drug therapies have proven insufficient in achieving the required results [5,6].

The combination of medicinal and non-medicinal treatment is essential to the maintenance of functional autonomy of movement [7]. Active exercises combined with muscle strengthening and stretching as well as improvements in physical fitness through aerobic exercise [7,8] are the main treatment options for patients with OA of the knee.

Low-level laser therapy (LLLT) has properties that exert a positive influence on the proliferation of fibroblasts, collagen synthesis, and bone regeneration. LLLT also has an analgesic effect mediated by hormonal and opioid mechanisms and has therefore recently become an important tool in the treatment of OA, offering pain relief and improved knee function [9,10]. The use of phototherapy in the form of LLLT and light-emitting diode therapy, both of which operate in the red and infrared spectra, has proven effective in delaying the development of fatigue and improving muscle performance [11]. It would therefore seem advantageous to combine these two forms of phototherapy in a single device. However, clinical trials are needed to test the effects on deeper structures, such as joints, using comparable protocols and outcome measures. Due to its physiological effects, phototherapy may promote increased positive effects of preexisting treatments and may slow the degeneration process and its repercussions, such as contractures and joint deformity, which can lead to postural imbalance and the loss of muscle strength in the lower limbs, resulting in recurrent falls.

The aim of the proposed study is to analyze the effect of the incorporation of phototherapy into a therapeutic exercise program for OA of the knee. The hypothesis is that patients with OA of the knee who are treated with phototherapy combined with a therapeutic exercise program will experience a greater reduction in pain as well as improved knee range of motion, static balance, functional capacity, muscle strength, and quality of life in comparison with those treated with exercise alone.

## Methods/Design

### Overview of research design

We propose a double-blind, placebo-controlled, randomized clinical trial to analyze the effect of the incorporation of phototherapy into a therapeutic exercise program for individuals with osteoarthritis of the knee. Participants will be recruited from clinics and hospitals and will be allocated to different groups through a randomization process using opaque envelopes containing cards stipulating one of the three following groups: 1) exercise program, 2) exercise program + phototherapy, and 3) exercise program + placebo phototherapy. Phototherapy will be performed on the knees diagnosed with OA.

The study will be divided into two evaluations and one treatment phase, to which all individuals will be submitted. Phase one is the initial evaluation phase. After recruitment, individuals who meet the eligibility criteria will undergo an initial evaluation in the following sequence: administration of the Lower Extremity Functional Scale (LEFS), the WHOQOL-BREF questionnaire and the Western Ontario and McMaster Universities Index for Osteoarthritis (WOMAC), numeric pain rating scale (NPRS) and algometry for pain, followed by a functional evaluation (stabilometry, dynamometry, range of motion (ROM), timed up-and-go test (TUGT) and the functional reach test (FRT)). Phase two is the treatment phase. Following randomization, the treatments will be performed on the knee(s) in three weekly sessions spanning eight weeks (for a total of 24 sessions). Phase 3 is the final evaluation phase. One day after the end of the treatment phase, the final evaluation will be performed, following the same sequence employed in the initial evaluation (Additional file 1).

### Blinding

The participants in exercise program + phototherapy and exercise program + placebo phototherapy will be blinded to the form of treatment (active or placebo phototherapy). The researcher in charge of the randomization process will program the phototherapy device based on the randomization results and will then turn the device over to another researcher for application. Three other researchers blinded to the phototherapy protocol will individually be in charge of the procedures in each group. These researchers will not participate in the evaluation phases. The evaluations will be carried out by a fourth researcher blinded to the allocation of the participants to the different groups. The statistician will be blinded to the allocation and procedures until the conclusion of the statistical analysis.

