#### Exercise program

The program will include three weekly 45 to 60-minute sessions over the course of eight weeks (24 sessions) and will be organized in three phases: 1) weeks one to two, improvements in balance and coordination, each exercise will have 30 repetitions and two sets; 2) weeks three to five, each exercise will have 20 repetitions and three sets; and 3) weeks six to eight, each exercise will have 20 repetitions and three sets [28].

Phase 1: 10 minutes of warm up on a treadmill; participant seated with weight on ankle extends the knee and performs internal and external rotation on each leg; in the supine position on a cot, from maximum knee flexion, the participant slowly performs maximum knee extension on each leg; in the standing position, the participant flexes the knee to 60° and performs knee extension; the participant walks along a three-meter line; if the participant steps outside the line, he/she must return to the initial position and in the standing position, the participant transfers weight from one leg to the other.

Phase 2: In the standing position, the participant flexes the knee to 60° and performs knee extension; the participant walks sideways crossing the legs to the right and to the left; in the standing position, the participant maintains his/her balance on a balance board; In the supine position on a cot, the participant performs maximum knee flexion on each leg;in the standing position, the participant positioned on a step flexes one knee and squats, followed by extension; the same is performed with the other leg.

Phase 3: The participant walks sideways crossing the legs to the right and to the left; in the standing position, the participant flexes the knee to 60° on each leg; in the standing position, the participant maintains his/her balance on a balance board; the participant is then asked to close his/her eyes; in the standing position, the participant holds the toes flexed for 1 to 2 seconds; participant seated with weight on ankle extends the knee and performs knee extension, holds for 3 to 4 seconds and returns slowly to flexion on each leg.

For exercises involving weight, the weight will be determined for each participant using the ten-maximum repetition test. New tests will be held at the beginning of each phase.

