#### Data analysis

The sample size was calculated using the MVIC of the muscles as the outcome and an 80% power to detect a 20% improvement, with a 5% level of significance. Based on the study by Alfredo *et al.*[28], a minimum of 17 patients were determined for each group.

Primary (MVIC of the muscles (dynamometer) and stabilometry) and secondary (pain (digital algometer), range of motion (fleximeter), and quality of life (WHOQOL-BREF and WOMAC ) outcomes will be assessed.

Descriptive statistics will be used, and data will be summarized using mean, standard deviations, and percentiles. Normality of data distribution will be tested using the Kolmogorov-Smirnov test. Normal variables and comparison among three groups of the study will be assessed at baseline and at eight weeks follow-up using Analysis of Variance. Post-hoc tests will consist of the Turkey test for parametric variables, and the Dunn’s test for non-parametric variables, and the Dunn’s test for non-parametric variables. Data processing will be performed using the SPSS™ version 13.0 (Chicago, Illinois, United States) and the level of significance will be set to 5%.

The Cohen's d method will be used to determine the effect size. The interpretation of the values will be based on the classification established by Cohen: less than 0.2 (small effect); around 0.5 (moderate effect), up from 0.8 (large effect) [29].

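### On the plain reading one researcher runs each group, so the treating person is confounded with treatment unless rotation is stated

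*Protocol article*

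**What the plan says.** The protocol article, Overview of research design, defines three arms: "1) exercise program, 2) exercise program + phototherapy, and 3) exercise program + placebo phototherapy". Every arm receives the exercise program, in three sessions a week for eight weeks (24 sessions). The Exercise program section puts each session at 45 to 60 minutes.

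The Blinding section describes who does what. The researcher who handles randomization programs the device and "will then turn the device over to another researcher for application". It continues: "Three other researchers blinded to the phototherapy protocol will individually be in charge of the procedures in each group". These people take no part in assessment: "The evaluations will be carried out by a fourth researcher blinded to the allocation of the participants to the different groups". The article mentions no rotation of treating researchers between arms and no allocation within researcher.

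The Data analysis section names two primary outcomes, muscle strength (MVIC by dynamometer) and stabilometry. It compares the three groups by ANOVA and mentions no researcher term. The sample size statement is that "a minimum of 17 patients were determined for each group".

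**The concern.** There are three treating researchers and three groups, each researcher is individually in charge, and the evaluator is counted as the fourth. Read plainly, each arm has its own supervisor. Any difference between supervisors in correction, motivation, pacing or rapport over 24 sessions then falls entirely on one arm and looks the same as a treatment effect.

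The placebo arm is there to isolate the effect of the light. Under this arrangement, active versus placebo also compares one researcher with another. Strength after supervised training could plausibly depend on who does the training, and balance may too. The planned standard errors reflect variation between patients only, so a significant difference could come from the supervisor. This is settled by how treatment is delivered, and a later analysis plan could not repair it.

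**Working it through.** **1. The plan's own figure.** The stated basis is "an 80% power to detect a 20% improvement, with a 5% level of significance", giving 17 per group. No mean or SD is given, so 17 cannot be reproduced directly, only back-solved. With n = 2(z₁₋α/₂ + z₁₋β)²/d², a two-sided test gives d = √(2/17) × (1.960 + 0.842) = 0.96, which means an SD of 20/0.96 = 20.8% of the mean. The exact t test gives d = 0.99, and a one-sided normal calculation gives 0.85. For an SD of 15%, 20%, 25% or 30% of the mean, n per group would be 9, 16, 25 or 36. The confounding does not depend on this. Only n = 17 is used below, with d as a yardstick.

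**2. Can the two effects be separated?** Take 51 participants (3 × 17) and a model with an intercept, two group terms and two researcher terms (five columns).
- One researcher per group: group and researcher indicators are identical, and the matrix has rank 3 of 5. No researcher effect can be estimated apart from group.
- Each researcher treats in all groups: rank 5 of 5. Both can be estimated.

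**3. Effect on the error rate.** Let ρ be the share of outcome variance due to the researcher. The article gives no value, so 0 to 0.10 is an assumption. With one researcher per group, the true variance of a group mean, relative to what the test assumes, is

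inflation = [ρ + (1−ρ)/n] / [(1−ρ)/n] = 1 + nρ/(1−ρ), with n = 17.

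Example, ρ = 0.05: 1 + 0.85/0.95 = 1.895.

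The critical values are t = 2.037 (32 df) and F = 3.191 (2 and 48 df). The true type I error with no treatment effect is P(|t₃₂| > 2.037/√inflation) for two groups and P(F₂,₄₈ > 3.191/inflation) for three. For the F test with 2 and 48 df, P(F > x) = (1 + 2x/48)⁻²⁴. At ρ = 0.05, x = 3.191/1.895 = 1.684, so the probability is (1.0702)⁻²⁴ = 0.196.

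| Assumed ρ | Inflation | Two-group t test | Three-group ANOVA |
|---|---|---|---|
| 0 | 1.000 | 5.0% | 5.0% |
| 0.01 | 1.172 | 6.9% | 7.6% |
| 0.02 | 1.347 | 8.9% | 10.4% |
| 0.05 | 1.895 | 14.9% | 19.6% |
| 0.10 | 2.889 | 24.0% | 34.0% |

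A simulation of 40,000 trials agrees: 6.9%, 8.8%, 14.6% and 24.0% for two groups, and 7.7%, 10.5%, 19.5% and 33.6% for the ANOVA, at ρ = 0.01 to 0.10. The two-group column is an unadjusted t test, so it is not the exact error rate of the planned post hoc tests. The formula uses only n and ρ, so it holds for MVIC and for stabilometry, each with its own unknown ρ.

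**4. Scale.** At ρ = 0.05 the difference between two researchers alone has SD √(2 × 0.05) = 0.32 outcome SD, about a third of the 0.99 SD that 17 per group can detect. The term 2ρ does not shrink as n grows, so recruiting more patients would not help.

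**The case against.** The wording is loose, and a reader might infer more than it supports: that one person delivers every session in an arm, never meets another arm, and that the trial is therefore certainly and fully confounded. The article does not go that far. Being in charge of procedures is not the same as delivering every session. The person who receives the programmed device may be one researcher serving both phototherapy arms, since the three in charge are introduced as others. All three are called blinded to the phototherapy protocol, which has little meaning for someone who only ever runs exercise alone. That could be taken as a second defect, but it could equally mean that fixed arms were not intended, so it settles nothing.

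There are also safeguards. The Exercise program section fixes exercises, repetitions, sets and phases, and ties load to a ten-repetition-maximum test repeated at each phase, so loading is not left to the supervisor's taste. Verbal encouragement during strength testing belongs to the evaluation, which the blinded fourth researcher carries out.

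What stands: one researcher per group is still the plainer reading, and nothing describes crossing. If one person applied the device in both phototherapy arms, supervision of the exercise would still be tied to the arm unless crossing is stated. A fixed program narrows differences in coaching and rapport without removing them. Blinded assessment protects the measurement; it does not make three supervisors equally effective.

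**Conclusion.** As written, the Blinding section ties the supervising researcher to the arm, and that confounding reaches the active versus placebo comparison. If the reading is right, the failure to separate the two effects follows from the design alone and needs no assumed figure.

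The size does rest on assumption. Over a researcher share of 0% to 10% of variance, the true error of a nominal 5% test runs from 5% to about 24% for two groups and 34% for the ANOVA. A reader might take the upper figures as the trial's error rate. The article does not support that: it gives no variance share, the standardised program may keep the share small, and zero is within the range. The percentages are also averages over hypothetical researchers. In the trial itself the three effects are fixed and act as a bias of unknown size and direction.

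This is a should-fix point, held with moderate confidence because the sentence could be clarified the other way.

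**What to change.** Have the same three researchers each treat participants from all three groups in roughly equal numbers, about 17/3, so five or six per researcher and group. Randomizing within researcher would achieve this. At minimum, cross them over the two phototherapy groups. That protects active versus placebo, but comparisons with exercise alone would still mix treatment and researcher. Keep the device settings coded by the researcher who handles randomization, and add researcher as a factor to the planned analysis model. In a three-group ANOVA this costs two residual degrees of freedom (48 to 46).

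The Trial status section says recruitment is under way, so the change should come early. Leave participants already treated as they are and record the changeover date. Those treated under the fixed arrangement cannot be disentangled afterwards.

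If delivery cannot be changed, report each group contrast as treatment plus researcher. If the researchers already rotate, correct the Blinding section and include researcher in the model.

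The cost is rostering work and a protocol amendment, with the same staff, sessions and devices. There is a small risk that a researcher who handles both settings could compare them, which is why the settings must stay coded. The article does not say whether they can be told apart in use.

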### Inclusion criteria

The inclusion criteria are as follows: diagnosis of OA of the knee (bilateral) confirmed by the participant’s physician according to criteria of the American College of Rheumatology; Grades 2 to 4 on the Kellgren-Lawrence OA scale (0 = absence of OA, 1 = doubtful, 2 = minimal, 3 = moderate, and 4 = severe); aged between 40 and 80 years; either gender; and knee pain and functional disability for at least three months, as confirmed by the medical history of each patient. The participants will be allowed to use medications prescribed by their doctor. The use of analgesics or anti-inflammatory drugs will be monitored throughout the study. The name, dosage, and frequency of the medications will be recorded and presented in a table.

### Exclusion criteria

The exclusion criteria are as follows: a history of trauma to the knees; cognitive or psychological disorder; neurological disorder (sensory or motor); cancer; diabetes; acute adverse health condition; symptoms of OA of the hip; cardiopulmonary disease that impedes walking; need for a wheelchair or gait-assistance device; received steroids through intra-articular injection or orally in the previous six months; or received physical therapy treatment for the knee within last four weeks. The exclusion criteria will be determined by access to the medical history of individuals.

### Ethics and data security

This trial received approval from the Human Research Ethics Committee of University Nove de Julho (Brazil) under process number 525.849, dated 10 February 2014. All individuals will be asked to provide written informed consent prior to randomization using a standard form. This trail is registered with the World Health Organization at ClinicalTrials.gov under number NCT02102347 on 29 March 2014.

### Procedures

#### Questionnaires and scales

The following questionnaires and scales will be administered before and after the treatment protocols: Lower Extremity Functional Scale: Scale consisting of 20 items developed to evaluate musculoskeletal dysfunction in the lower limbs [12]. The scores for each item are 0 (extreme difficulty or unable to perform the activity), 1 (quite a bit of difficulty), 2 (moderate difficulty), 3 (a little bit of difficulty), and 4 (no difficulty). The maximum score is 80 points [13]. Numeric pain rating scale: A simple, easily administered scale made up of a set of numbers ranging from 0 (absence of pain) to 10 (worse pain imaginable) [14]. The degree of pain in the knee(s) with OA will be measured with the participant at rest, before the use the algometry. Quality of life will be evaluated using the WHOQOL-BREF, which is a short version of the WHOQOL-100 developed by the Quality of Life Group of the World Health Organization. The WHOQOL-BREF is made up of 26 items: two addressing overall health and the others divided among four subscales (physical health, psychological health, social relations, and environment). Each item is scored based on a Likert scale ranging from 1 to 5 points. At the end of the study, the results will be transformed into a linear scale ranging from 0 to 100, with higher scores denoting a better quality of life [15,16]. Besides being administered during the initial and final evaluations, the WHOQOL-BREF will also be administered three and six months after the final evaluation through telephone contact.The WOMAC is a specific index for the evaluation of pain, stiffness, and physical function in individuals with OA of the knee and/or hip. This index offers separate scores for the different subscales and contains 24 items: five on pain (score: 0 to 20); two on stiffness (score: 0 to 8), and 17 on physical functioning (score: 0 to 68) [17]. Higher scores indicate worse pain, stiffness, and functional limitation. All questionnaires and scales will be administered in a private room and the participants will be instructed to fill out all items. If a participant refuses or is incapable of cooperating, the researcher will mark the exam with the letters ‘NR’, denoting ‘not registered’, and will also write down the reason for the refusal or inability to complete the questionnaire. All assessment tools will be administered without time constraints to avoid the occurrence of rushed responses.

